### Groups and interventions

2.2

Participants will be allocated to one of two non-randomized, parallel groups based on their acceptance to use the wearable device:
Intervention Group – AI-Based Remote Monitoring: Patients in this group will wear wearable devices continuously over a six-month period. The wearable device collects multimodal biometric data, including SpO₂, HRV, EDA, respiratory rate, skin temperature, pulse rate, and sleep metrics (actigraphy). These data are automatically transmitted to the SMART-CARE platform, where advanced AI algorithms analyse trends and detect early signs of clinical deterioration. In case of abnormal findings, the system generates alerts for the clinical team, which may initiate teleconsultations, therapy adjustments, or in-person evaluations to prevent acute decompensation.Control Group – Standard Clinical Follow-Up: Participants in the control group will receive standard CHF management in accordance with current European Society of Cardiology (ESC) guidelines. This includes outpatient visits every three months, ECG and echocardiographic assessments, and laboratory evaluations. No remote monitoring will be applied in this group. Clinical decisions, including medication adjustments, will be based on periodic clinical evaluations and patient-reported symptoms.

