### Outcomes

2.4

Both groups will undergo assessments at baseline, 3 months, and 6 months, including evaluations of functional status, echocardiographic parameters, biochemical markers (e.g., BNP, NT-proBNP, renal function), and quality of life assessed using the Kansas City Cardiomyopathy Questionnaire (KCCQ) (36–39) (Table 2).

**Table 2 T2:** SMART-CARE outcome measures by timepoint.

Outcome type	Outcome measure	Domain	Baseline	3 months	6 months
Primary	Change in Hospital Admissions	Clinical Events			✔
Secondary	Change in Quality of Life (KCCQ Score)	Quality of Life	✔	✔	✔
Secondary	Adverse Effects of CHF Therapy	Safety			✔
Secondary	Change in BNP Levels	Biochemical	✔	✔	✔
Secondary	Change in NT-proBNP Levels	Biochemical	✔	✔	✔
Secondary	Change in Serum Creatinine	Biochemical	✔	✔	✔
Secondary	Change in eGFR	Biochemical	✔	✔	✔
Secondary	Change in Serum Sodium	Biochemical	✔	✔	✔
Secondary	Change in Serum Potassium	Biochemical	✔	✔	✔
Secondary	Change in Serum Chloride	Biochemical	✔	✔	✔
Secondary	Change in HRV	Functional (ECG)	✔	✔	✔
Secondary	Change in Respiratory Rate	Functional (ECG)	✔	✔	✔
Secondary	Change in LVEF	Echocardiographic	✔	✔	✔
Secondary	Change in E/A Ratio	Echocardiographic	✔	✔	✔
Secondary	Change in LV End-Diastolic Volume	Echocardiographic	✔	✔	✔
Secondary	Change in LV End-Systolic Volume	Echocardiographic	✔	✔	✔

CHF, chronic heart failure; KCCQ, Kansas City Cardiomyopathy Questionnaire; BNP, B-type Natriuretic Peptide; NT-proBNP, N-terminal pro-B-type Natriuretic Peptide; eGFR, estimated Glomerular Filtration Rate; HRV, Heart Rate Variability; ECG, Electrocardiogram; LVEF, Left Ventricular Ejection Fraction; E/A Ratio, Early to Late Ventricular Filling Velocity Ratio; LV, left ventricle.

The primary outcome of the SMART-CARE study is the relative reduction (≥20%) in hospital admissions, including emergency department visits and unplanned hospitalizations, over a six-month follow-up period in the intervention group compared to standard care (40). Hospitalization data will be collected prospectively and analysed for frequency, duration, and cause.

Secondary outcomes include:

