Quality of Life (QoL): Measured using KCCQ at baseline, 3 months, and 6 months.Biochemical parameters: BNP, NT-proBNP, serum creatinine, eGFR, and serum electrolyte levels (sodium, potassium, chloride) at 3 and 6 months.Functional parameters: Variations in HRV and RR derived from wearable sensor data.Echocardiographic measures: LVEF, Early to Late Ventricular Filling Velocity Ratio (E/A ratio), and left ventricular end-diastolic and end-systolic volumes, measured at 3 and 6 months.Adverse events: Incidence of therapy-related complications such as hypotension and bradyarrhythmias.These outcomes will provide a comprehensive evaluation of the impact of AI-driven remote monitoring clinical status, functional performance, biomarker trends, and patient-reported outcomes in individuals with CHF. The measurements collected by the minimally invasive devices will be uploaded to the “Smartcare” platform and analyzed using machine learning (ML) techniques to develop multiparametric scores capable of identifying the specific trajectory of patients affected by HF.

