## Expected results

3

We anticipate that AI-based remote monitoring with the integration of wearable devices will lead to a ≥20% reduction in hospital admissions over six months compared to standard care. Furthermore, we expect improvements in secondary outcomes, including enhanced quality of life, reduced therapy-related adverse events, and more favourable trends in biochemical and echocardiographic parameters. By enabling early detection of clinical deterioration and supporting timely intervention, the SMART-CARE system is expected to offer a more proactive, individualized, and data-driven approach to managing CHF. These findings may support the integration of wearable technologies and AI into routine clinical practice for heart failure patients, potentially reducing the burden on healthcare systems and improving long-term patient outcomes.

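### Heart rate variability and respiratory rate are given two conflicting sources, one of which the control group does not have

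*Protocol article*

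**What the plan says.** **Heart rate variability (HRV) and respiratory rate (RR).** The list of secondary outcomes in section 2.4 reads: "Functional parameters: Variations in HRV and RR derived from wearable sensor data". Table 2 in the same section places both under the domain "Functional (ECG" (the closing bracket is left off here), with ticks at baseline, 3 and 6 months. The sentence that introduces the table says: "Both groups will undergo assessments at baseline, 3 months, and 6 months".

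**Who wears the device.** Section 2.2 says of the intervention group: "Patients in this group will wear wearable devices continuously over a six-month period". Of the control group it says: "No remote monitoring will be applied in this group". Control follow-up is described thus: "This includes outpatient visits every three months, ECG and echocardiographic assessments, and laboratory evaluations".

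**Adverse events.** Section 2.4 defines the safety outcome as "Incidence of therapy-related complications such as hypotension and bradyarrhythmias", and Table 2 ticks it once, at 6 months. It does not say how events are found. Section 3 expects "reduced therapy-related adverse events" with monitoring.

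**The concern.** A secondary outcome that is compared between groups has to be measured in both, by the same method. The text of section 2.4 and Table 2 name different sources for HRV and RR, and the source named in the text exists in one group only. Someone building the case report form from the text would collect nothing for controls. Someone trying to satisfy both statements might pair wearable values in one group with ECG values in the other. Visit recordings that are not taken in controls cannot be recovered afterwards, so the conflict needs settling before data collection and not at analysis.

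The safety outcome raises a related but weaker question. Bradyarrhythmia and hypotension are findings that pulse monitoring, home devices and extra clinical contacts can bring to light, and only the intervention group has these. If such findings count as events, the comparison partly reflects how closely each group was watched.

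**Working it through.** **1. Number of outcomes affected.** Table 2 lists 15 secondary outcomes: KCCQ, adverse effects, BNP, NT-proBNP, creatinine, eGFR, sodium, potassium, chloride, HRV, RR, LVEF, E/A ratio, and two left ventricular volumes. HRV and RR are 2 of these 15.

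**2. The possible readings of the HRV/RR source.**

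- *Wearable, as in the section 2.4 text.* Controls wear no device (section 2.2), so the number of controls with a value is 0 and no between-group comparison exists.
- *Wearable in one group, ECG in the other.* The observed difference is the group effect plus the method effect, and every patient's method is fixed by group. The covariate adjustment and propensity matching of section 2.6.1 balance patient characteristics. They cannot separate method from group, because neither group is measured by the other's method. Analysing change from baseline removes a constant offset between methods, but not a proportional one: if one method reads k times the other, its changes are k times as large too.
- *ECG in both groups, as in Table 2.* The comparison is valid in principle, but it contradicts the section 2.4 text.

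Only the third reading gives a usable comparison. The article names visit ECGs explicitly for controls (sections 2.1 and 2.2). For the intervention group they follow from Table 2 and the schedule for both groups. It does not say whether the recording is long enough to yield HRV and RR.

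**3. Opportunity to detect adverse events.**

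- Intervention group: pulse rate among the device signals (section 2.2); blood pressure monitors among the complementary home devices (section 2.3); alerts that lead to prompt clinical assessment (section 2.5).
- Control group: three-monthly visits, with management guided by those visits and by the symptoms patients report (section 2.2).

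**4. Illustration only.** The documents give no detection rates or event risks, so every input here is assumed: equal true risk of 10%, 20% or 30% in both groups, 150 patients per group (an equal split of 300), and 90% of events detected with monitoring.

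Apparent risk ratio = detection with monitoring / detection in controls.

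| Detected in controls | Apparent ratio | Chance of a significant excess with the device, two-sided 5% test, at true risk 10% / 20% / 30% |
|---|---|---|
| 90% | 0.9/0.9 = 1.00 | nominal error rate (5% two-sided) |
| 70% | 0.9/0.7 = 1.29 | 0.093 / 0.155 / 0.228 |
| 50% | 0.9/0.5 = 1.80 | 0.273 / 0.515 / 0.725 |

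On the same assumptions, the true reduction that would be exactly hidden is 1 − 0.7/0.9 = 22% in the second row and 1 − 0.5/0.9 = 44% in the third.

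**The case against.** **Table 2 may settle the source.** Both groups are assessed at the three visits, the table says ECG, and controls have ECGs. This stands in part. A reader might infer that the two outcomes certainly have no valid comparator, or that group and method are already fully confounded. The documents do not establish either: the first follows only from the text of section 2.4, and the second needs a mixed-source analysis that is nowhere specified. What remains is two statements in one section that cannot both define the outcome.

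**A between-group comparison may not be intended.** HRV and RR are absent from the benefits anticipated in the abstract and in section 3, and section 2.6.2 names only paired or repeated-measures tests for continuous variables. But section 2.4 presents the outcomes as evaluating the impact of monitoring, Table 2 sits under assessments in both groups, and nothing marks these two as intervention-only.

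**The adverse-event point is inference.** This stands. A reader might conclude that adverse events are sought continuously in one group only and that the safety comparison is therefore biased against the device. The article does not say so. No passage makes device signals a source of adverse events, and Table 2 draws no distinction by group. Blood pressure is not among the continuously recorded signals listed in sections 2.1 and 2.2, and the home monitors have no stated frequency. The Introduction describes a device capable of real-time blood pressure but gives no study schedule for it. Rules for finding events may sit in the full protocol, which is not shown.

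**Conclusion.** The HRV/RR source is contradictory as written and must be reconciled. It affects 2 of the 15 secondary outcomes and leaves the primary outcome untouched. This rests on the article's own wording and on no assumed figure.

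The adverse-event point holds only as a risk. The monitored group plainly has more opportunity for detection, more clearly for bradyarrhythmia than for hypotension. Whether that becomes bias depends on ascertainment rules the article does not describe. If it does, it would tend to add events in the intervention group, so that an increase might be artefact and a null result might hide a real reduction. An observed reduction would, in that case, be conservative and still interpretable. The ratios of 1.29 and 1.80 are consequences of assumed detection rates and are not estimates for this trial.

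**What to change.** **HRV and RR.** Correct the section 2.4 text so that between-group HRV and RR come from the same standardised visit recording in both groups at baseline, 3 and 6 months, in line with Table 2. Report wearable HRV and RR as descriptive data for the intervention group only.

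*Cost:* a wording change, plus confirmation that the visit ECG is taken in both groups and is long enough to yield both measures. If the planned recording is too short, it has to be lengthened at three visits per patient.

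**Adverse events.** Add a case report form field for how each event was detected. Base the between-group comparison on events ascertained at the scheduled visits common to both groups, and tabulate device- or alert-detected events separately. Do not use medical contact or a treatment change as the common criterion: sections 2.2 and 2.5 have alerts leading to contact, and section 2.2 to therapy adjustment, so that criterion would bring the imbalance back.

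*Cost:* one field and one extra table. Events found only between visits drop out of the formal comparison but are still reported.

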### Safety management and contingency planning

2.5

An additional strength of the SMART-CARE design lies in the structured approach to emergency management. The platform is not limited to early detection but also integrates a predefined pathway to ensure patient safety in the event of acute clinical deterioration. Alerts generated by abnormal biometric trends prompt immediate evaluation by the clinical team, who can escalate the response according to severity—ranging from direct patient contact or urgent teleconsultation to expedited in-person assessment or activation of local emergency medical services (EMS, 112/118 in Italy). This structured hospital–community network ensures rapid intervention and continuity of care, thereby minimizing the risk of adverse outcomes and reinforcing the overall safety and feasibility of AI-driven remote monitoring in real-world settings.

In addition, a technical contingency plan is in place: in case of device malfunction, connectivity issues, or platform failure, patients are promptly supported by remote technical assistance, with the possibility of temporary transition to standard in-person care to guarantee uninterrupted clinical follow-up. All participants undergo structured onboarding, including device training and safety instructions, and those with limited digital literacy are required to have caregiver support; continuous technical and clinical assistance is available throughout the study period. Furthermore, all clinical and biometric data are transmitted and stored in secure, encrypted repositories, ensuring data protection, traceability, and real-time safety oversight. This integrated safety and contingency framework is designed to minimize clinical risks, enable rapid response to emergencies, and maintain high standards of care within a remote monitoring setting (Figure 3).

**Figure 3 F3:**
[figure not shown]
SMART-CARE emergency management pathway. The right panel summarizes cross-cutting safety measures (technical contingency, training and support, data security) that are active across all phases of the clinical workflow.

### Statistical analysis

2.6

#### Primary endpoint analysis

2.6.1

To assess the primary endpoint of the study, Kaplan–Meier survival curves will be constructed to compare the time to first hospitalization between groups. Group differences will be evaluated using the log-rank test. Subsequently, a Cox proportional hazards regression analysis model will be performed to examine the association between the variable “Device Use (Yes vs. No)” and the reduction in hospital admissions. The model will be adjusted for all statistically significant covariates identified through ANOVA between the two groups. To mitigate selection bias resulting from the non-randomized design, propensity score methods will be applied. The propensity score will be estimated using baseline variables including age, sex, LVEF phenotype, NYHA class, major comorbidities (hypertension, atrial fibrillation, diabetes mellitus, COPD/OSA, obesity), prior HF hospitalizations, baseline biomarkers (BNP/NT-proBNP, renal function, electrolytes), and key echocardiographic indices (LVEF, LV volumes). A 1:1 nearest-neighbour matching approach without replacement will be used. Covariate balance between groups will be evaluated using standardized mean differences (SMD), with values <0.10 indicating adequate balance. Results will be expressed as hazard ratios (HR) with corresponding 95% confidence intervals (CI).

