**Methods:**

SMART-CARE is a prospective, multicenter, observational cohort study enrolling 300 adult patients with CHF (HFrEF, HFmrEF, or HFpEF) across three Italian tertiary centers. Participants are assigned to an intervention group, using wrist-worn, chest-worn, and multiparametric CE-certified wearable devices for six months, or to a control group receiving standard CHF care. Physiological data (e.g., SpO₂, HRV, respiratory rate, skin temperature, sleep metrics) are continuously collected and analyzed in real time through AI algorithms to generate alerts for early clinical intervention. The primary endpoint is a ≥20% reduction in hospital admissions over six months. Secondary outcomes include changes in quality of life (Kansas City Cardiomyopathy Questionnaire), biomarkers (BNP, NT-proBNP, renal function, electrolytes), echocardiographic indices (LVEF, LV volumes), and safety events.

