#### Handling of missing data and dropouts

2.6.4

Missing data and incomplete follow-up will be handled according to established recommendations for observational cohort studies. For clinical, biochemical, and echocardiographic variables, the pattern and mechanism of missingness will be evaluated. When data are missing at random (MAR), multiple imputation using chained equations (MICE) will be applied to reduce bias and preserve statistical power. In case of non-random missingness, sensitivity analyses will be performed using complete-case analysis and worst-case/best-case scenarios. For time-to-event analyses, dropouts will be treated as censored observations at the last available follow-up. Device adherence will be quantified as the percentage of monitoring days with valid wearable data; predefined thresholds for minimum acceptable adherence will be applied in sensitivity analyses. Per-protocol and intention-to-monitor analyses will be conducted to assess the robustness of the findings with respect to missing data and incomplete device use.

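### The primary endpoint and the sizing concern the rate of all admissions including ED visits, but the only stated primary analysis is time to first hospitalization

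*Protocol article*

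**What the plan says.** **Endpoint.** The Abstract (Methods) says: "The primary endpoint is a ≥20% reduction in hospital admissions over six months". Section 2.4 defines the primary outcome as "the relative reduction (≥20%) in hospital admissions, including emergency department visits and unplanned hospitalizations, over a six-month follow-up period in the intervention group", compared with standard care, and adds: "Hospitalization data will be collected prospectively and analysed for frequency, duration, and cause".

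**Sizing.** Section 2.6.3 assumes a 20% relative reduction in the rate of hospital admissions, again with ED visits included. It uses two-sided alpha 0.05 and 85% power, and arrives at 186 participants, 205 after dropout, with 300 to be enrolled. It gives no control-group rate.

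**Analysis.** Section 2.6.1, which sets out the primary endpoint analysis, uses Kaplan–Meier curves "to compare the time to first hospitalization between groups". It continues: "Group differences will be evaluated using the log-rank test". A Cox model for device use follows and is described as examining the reduction in hospital admissions; results are reported as an HR with a 95% confidence interval. The section contains no count, rate or recurrent-event model, no mention of ED visits and no reference to 20%. The only decision criterion in the article is two-sided p < 0.05, at the end of section 2.6.2.

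**The concern.** Endpoint and sizing agree with each other; the analysis is the part that differs. It does so in three ways.

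- **First event versus all events.** A patient admitted four times counts the same as one admitted once at the same time. Eligibility requires a hospitalization or an outpatient visit with intravenous therapy for heart failure in the previous 12 months (Table 1), so repeat events are plausible.
- **ED visits.** They are part of the endpoint and the sizing but are not named in the analysed event. This matters here: alerts can lead to in-person evaluation or emergency services (sections 2.2 and 2.5), and section 5 concedes that false positives may raise healthcare use. If the device lowered first hospitalizations but raised ED visits, the endpoint would count the increase, while the analysis as worded might not.
- **The 20%.** It is written into the endpoint, but a log-rank test judged at p < 0.05 addresses only whether the hazards differ.

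At stake is whether the reported primary result is the pre-stated quantity, and whether the event definition and effect measure are fixed before the data are seen.

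**Working it through.** **1. The plan's own figure.** The 186 cannot be reproduced, because no control rate is given. The step to 205 is 186 × 1.10 = 204.6. As a rate comparison without overdispersion, the number per arm is (1.960 + 1.036)² × (1/λ + 1/(0.8λ)) / (ln 0.8)² = 8.978 × (2.25/λ) / 0.0498 ≈ 405.7/λ, where λ is the number of control events per patient over six months. To get 93 per arm (186 in total) requires λ ≈ 405.7/93 ≈ 4.4. This is a separate problem, noted here only because it limits what the fix can achieve.

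**2. What the first-event HR shows when the true rate ratio is 0.80.** Assumed inputs: gamma-Poisson counts with mean μ per control patient over six months and dispersion k.

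- Probability of at least one event: P = 1 − (1 + kμ)^(−1/k).
- Share of events that are first events: P/μ.
- First-event HR, taken as the ratio of cumulative hazards at six months: ln(1 + 0.8kμ) / ln(1 + kμ).

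For k = 1:

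- μ = 0.5: P = 1 − 1/1.5 = 0.333; share 0.333/0.5 = 0.67; HR = ln 1.4 / ln 1.5 = 0.336/0.405 = 0.83.
- μ = 1.0: P = 1 − 1/2 = 0.50; share 0.50; HR = ln 1.8 / ln 2 = 0.588/0.693 = 0.85.

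| Dispersion k | μ | First events as share of all | HR when rate ratio is 0.80 |
|---|---|---|---|
| 0 (Poisson) | 0.5 | 79% | 0.80 |
| 0 (Poisson) | 1.0 | 63% | 0.80 |
| 1 | 0.5 | 67% | 0.83 |
| 1 | 1.0 | 50% | 0.85 |
| 1 | 2.0 | 33% | 0.87 |
| 2 | 0.5 | 59% | 0.85 |
| 2 | 1.0 | 42% | 0.87 |
| 2 | 2.0 | 28% | 0.89 |

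The attenuation comes from heterogeneity between patients. Events are left unused in every row.

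**3. Significance versus a 20% reduction.** Assume 300 patients, 150 per group, 40% of controls with a first event and a true HR of 0.80. First events: 150 × 0.40 + 150 × (1 − 0.6^0.8) = 60 + 50 = 110. SE(log HR) = 2/√110 = 0.191. Significance needs an observed HR of at most exp(−1.96 × 0.191) = 0.69. An upper 95% limit below 0.80 needs an observed HR below 0.80 × 0.69 = 0.55. These are different claims, and the analysis section mentions only the comparison with no difference.

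**4. Power under either repair (rate ratio or HR 0.80, 1:1).**

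- Rate ratio, one event per control patient, 150 per arm, Poisson: SE = √(2.25/150) = 0.1225; 0.2231/0.1225 = 1.82; power Φ(1.82 − 1.96) ≈ 44%.
- The same with k = 1: SE = √(4.25/150) = 0.168; 0.2231/0.168 = 1.33; power Φ(1.33 − 1.96) ≈ 26%.
- Log-rank: events needed for 85% power are 4 × 8.978/0.0498, about 722, more than 300 patients can supply as first events. With 20% to 60% of controls having a first event, power at 300 patients is about 13% to 30%. If all 300 had an event it would be about 49%.

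**The case against.** Several stronger readings are tempting, and the article does not support them.

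- **That the analysis cannot answer the study's question.** The aim at the end of the Introduction is whether monitoring can reduce hospitalizations, and a first-event HR bears on that. The attenuation to 0.83–0.85 is modest and vanishes without heterogeneity. This objection stands: the HR is informative, but it is not the endpoint's quantity.
- **That repeat admissions are discarded altogether.** Section 2.4 says the data will be analysed for frequency. That sentence names no method and is not carried into section 2.6.1, so the primary analysis still omits them.
- **That ED visits are excluded.** Section 2.4 itself uses hospitalization data as apparent shorthand straight after defining the broader event, and section 2.6.1 may do the same. Exclusion is not shown; the event is left unclear.
- **That the rate is plainly a count per patient.** Rate in section 2.6.3 could mean the proportion admitted, which would sit closer to a first-event analysis. Even so, the event named and the role of the 20% would need settling.
- **That there are two competing success rules.** No section says an observed 20% reduction means success. Section 2.6.3 uses 20% as the planning effect and section 3 as an expectation. The fault is that the endpoint wording builds the figure in.
- **That deaths count as favourable censoring.** Section 2.6.4 says only that "dropouts will be treated as censored observations at the last available follow-up". It concerns dropouts, and handling of death is commonly left to the analysis plan or full protocol.
- **That the Table 2 label "Change in Hospital Admissions" implies a change from baseline.** Section 2.4 states the between-group comparison, so this is a label only.

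**Conclusion.** The mismatch is in the text and does not depend on detail left to an analysis plan: endpoint and sizing concern the rate of admissions including ED visits, and the stated primary analysis is time to first hospitalization. Followed as written, the plan reports an HR for a different quantity, with an ambiguous event and no test of the 20% in the endpoint.

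The numerical size rests wholly on assumed event rates and dispersion. With k = 1 and 0.5 to 1.0 events per patient, a third to a half of events are unused and a true 0.80 reads as about 0.83 to 0.85. Across the wider range of k = 1 to 2 and up to 2 events per patient, it reads as 0.83 to 0.89. It should be put right before analysis, since the primary result would otherwise not be the pre-stated endpoint.

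**What to change.** Align endpoint, analysis and sizing in one of two ways.

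1. **Preferred.** Make the primary analysis the between-group rate ratio of all unplanned hospitalizations plus ED visits over six months. Use a negative binomial model with log follow-up time as offset, or a recurrent-event model with robust variance, with the planned confounding adjustment. Keep Cox on the first of ED visit or unplanned hospitalization as supportive.
2. **Alternative.** Redefine the primary endpoint as time to first ED visit or unplanned hospitalization, name both in section 2.6.1, and restate sizing and power on numbers of events.

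In either case, state that 20% is the planning effect and that success is a 95% confidence interval excluding 1 in favour of the device. If a reduction of at least 20% is to be claimed, state instead that the upper limit must be below 0.80.

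The cost is mainly wording, since hospitalization data are already collected prospectively; ED visits must be confirmed as captured in the same way. The first option needs a somewhat more complex model than a log-rank test. Neither restores the stated 85% power at 300 patients, so power must be restated separately with an explicit control rate.
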